## Abstract

Exercise training effectively mitigates aging-induced health and fitness impairments. Traditional training recommendations for the elderly focus separately on relevant physiological fitness domains, such as balance, flexibility, strength and endurance. Thus, a more holistic and functional training framework is needed. The proposed agility training concept integratively tackles spatial orientation, stop and go, balance and strength. The presented protocol aims at introducing a two-armed, one-year randomized controlled trial, evaluating the effects of this concept on neuromuscular, cardiovascular, cognitive and psychosocial health outcomes in healthy older adults. Eighty-five participants were enrolled in this ongoing trial. Seventy-nine participants completed baseline testing and were block-randomized to the agility training group or the inactive control group. All participants undergo pre- and post-testing with interim assessment after six months. The intervention group currently receives supervised, group-based agility training twice a week over one year, with progressively demanding perceptual, cognitive and physical exercises. Knee extension strength, reactive balance, dual task gait speed and the Agility Challenge for the Elderly (ACE) serve as primary endpoints and neuromuscular, cognitive, cardiovascular, and psychosocial meassures serve as surrogate secondary outcomes. Our protocol promotes a comprehensive exercise training concept for older adults, that might facilitate stakeholders in health and exercise to stimulate relevant health outcomes without relying on excessively time-consuming physical activity recommendations.

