In conclusion, it seems promising that agility training can serve as a feasible and time-efficient way to address a variety of health-related aspects relevant for the aging process. Numerous objective measures of neuromuscular, cardiovascular, cognitive and psychosocial origin can be challenged twice a week without excessive training volumes (which are not likely achievable by older adults). To our knowledge, no randomized controlled long-term intervention has applied the agility framework yet. Based on the above-mentioned rationales, we aim at introducing the protocol of an ongoing randomized controlled trial, investigating the effects of a one-year agility training intervention on neuromuscular performance, cardiovascular and cognitive functioning, as well as relevant psychosocial health outcomes in community-dwelling, healthy older adults. We specifically hypothesize that the agility training approach induces notable improvements in all physical performance measures (strength, balance, motor performance, aerobic capacity) after the one-year intervention period when compared to an inactive control group with at least moderate effect sizes that are comparable to other traditional training regimens. Secondly, we assume that those training effects will already be visible after six months of training with a further steady increase until the end of the one-year period. This study protocol was designed to contribute to a preventive multimodal training concept that can improve physical, cognitive and psychosocial health outcomes relevant to warrant healthy aging in an integrative and time-efficient way.

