### 2.3. Experimental Design

The study is designed as a one-year two-armed, randomized, controlled intervention trial (Figure 1). All participants were requested to sign a written informed consent after being informed about all study procedures and after adequate time for consideration. Group assignment was conducted, applying the minimization method [21]. Accordingly, all participants were stratified to the intervention or the control group (intervention: control = 1:1). Sex, age, maximum knee extension strength, dual task gait speed and peak oxygen consumption (VO2peak) served as strata for balanced group allocation. Couples were stratified to the same group due to infrastructural, motivational and interference issues. The number of couples was evenly balanced in both groups. Group assignment was communicated to the participants after baseline assessment via telephone. Participants of the intervention group receive two weekly training sessions for one year. The control group does not receive any treatments. Only a brief written recommendation for physical activity is sent out. They will be given the opportunity to take part in a training program once a week after the end of the study for 6 months. Both groups are to keep a logbook on falls, diseases/injuries and exercise over the entire one-year study period.

Primary and secondary endpoints are collected at pre- and post-testing. An additional interim test with only a few measurements is provided after six months of training. At baseline (T1) and at the post-assessment (T3) after one year, all measurements are performed. This includes neuromuscular, cognitive, cardiovascular and psychosocial tests. At the interim assessment (T2), only selected neuromuscular and psychosocial measurements are assessed for reasons of time and reasonableness. 

T1 also includes a medical anamnesis and physical examination to rule out some severe exclusion criteria in addition to the medical clearance. At T1 and at T3, three lab visits on non-consecutive days, each lasting one to two hours, are required for each participant. On day one, cardiovascular, pulmonary and sonographic assessments are completed. On day two, neuromuscular, cognitive and psychosocial measurements are conducted. On the third day of assessment, the Agility Challenge for the Elderly (ACE) takes place. The interim assessments (T2) are completed within 45 min.

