For assessing dual task gait speed, participants are instructed to walk an eight meter-long distance at their habitual, comfortable walking speed. Additionally, they are given a number between 100 and 110 and have to count backwards in steps of three aloud. The gait speed of three trials is measured with photoelectric time gates (DLS/F03, Sportronic, Leutenbach-Nellmersbach, Germany) and counts and errors are manually noted. The mean value of all three trials is used for data analysis. A very high reliability of this test was assessed for this test for healthy older adults (ICC = 0.93) [26].

The newly developed ACE serves as an agility-specific, functional assessment. The setup is conducted according to Lichtenstein et al. [27]. Prior to testing, participants undergo a standardized warm-up (slow and brisk walking, knee lifting, walking backwards, hip rotation). Then, the ACE is demonstrated once. Participants are instructed to pass through the course as fast as possible without running. They complete the ACE four times and the first trial serves as familiarization trial. Total time and split times of the three components of the ACE are measured with photoelectric time gates (DLS/F03, Sportronic, Leutenbach-Nellmersbach, Germany), providing high reliability values for total and split times (ICC = 0.84–0.94) and a coefficient of variation of 4%–6.7% [27].

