
### 2.9. Sample Size Estimation and Statistical Procedures

A sample size estimation was conducted with G*Power (Version 3.1, Heinrich Heine University, Duesseldorf, Germany). 68 participants (34 per group) are needed for statistical analysis, assuming moderate effects (f = 0.2) for training-induced changes in the primary outcomes (statistical power 90%, two-sided significance level α=.05). Expecting a realistic dropout rate of about 25%, a total of 85 participants were initially recruited.

Data entry will be double-checked and data ranges will be controlled for plausibility. Two researchers ([name]) will do data management and analysis. Independently conducted two-factorial repeated measured analyses of co-variance (rANOVA), with the respective endpoint as a baseline measure serving as the covariate [53], will be computed as primary analysis to assess the time course of adaptations between groups (factor 1: control group vs. intervention group; factor 2: time point of measurement; baseline, interim, post). The rANOVA interaction term between both factors is the main term of interest. Together with 90% confidence intervals, change scores from T1 to T3 and from T1 to T2 and T2 to T3 are calculated to arrive at an estimate of the size of the observed effects. The intention-to-treat analysis will be computed. The intention-to-treat analysis will be compared to as-treated analysis. Potential differences will be discussed.

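### Four primary endpoints are tested separately with an unsplit two-sided 0.05 and no stated success rule, so the false-positive rate depends on the claim made and the 90% power is a single-endpoint figure

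*Protocol article*

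**What the plan says.** The Abstract sets out four endpoints of equal rank: "Knee extension strength, reactive balance, dual task gait speed and the Agility Challenge for the Elderly (ACE) serve as primary endpoints". Section 2.5 describes them. For knee extension it singles out Fmax as the primary variable, as distinct from the rate of force development. For the ACE it makes no such choice: "Total time and split times of the three components of the ACE are measured with photoelectric time gates".

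Section 2.9 plans "Independently conducted two-factorial repeated measured analyses of co-variance (rANOVA"), each model adjusted for the baseline value of its own endpoint, with the group-by-time interaction as the term of main interest. The sample size sentence in the same section reads "68 participants (34 per group) are needed for statistical analysis", "assuming moderate effects (f = 0.2) for training-induced changes in the primary outcomes", with "statistical power 90%, two-sided significance level α=.05". Section 2.3 fixes the allocation ("intervention: control = 1:1").

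The article contains no hierarchy among the four endpoints, no division of alpha, no adjustment, and no statement of how many endpoints must succeed. The nearest text is the hypothesis in the Introduction, that the training "induces notable improvements in all physical performance measures (strength, balance, motor performance, aerobic capacity) after the one-year intervention period". This is a hypothesis, not a decision rule, and its list includes aerobic capacity, which is not a primary endpoint.

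**The concern.** With four separate primary tests, the error rate and the power of the trial's main conclusion depend on what counts as success. Two rules are common.

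- **Any one endpoint suffices.** The false-positive rate for the trial as a whole then exceeds 5% unless the tests are adjusted.
- **All four are required.** No adjustment is needed, but all four tests must succeed together, which is less likely than one test succeeding.

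The article does not say which rule applies, yet it publishes one alpha and one power figure for the primary outcomes collectively. Without a rule fixed in advance, one significant result out of four could later be presented as a positive trial. The 90% could also be read as the power of the trial's conclusion, when it belongs to a single test. The ACE adds a smaller ambiguity, because it yields a total time and three split times and none is named as primary.

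**Working it through.** **Inputs from the article.** Four primary endpoints (Abstract, section 2.5); f = 0.2, two-sided alpha 0.05, power 90%, N = 68 (section 2.9); two groups, 1:1 (section 2.3).

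**Assumptions, because the article does not give them.** The G*Power procedure is the repeated-measures within-between interaction; m = 2 measurements; repeated-measures correlation ρ = 0.5; a common correlation r among the four endpoint test statistics, varied from 0 to 0.9.

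**1. Reproduce the stated sample size.** The noncentrality is λ = f²·N·m/(1−ρ), with degrees of freedom (m−1) and (N−2)(m−1).

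- N = 68: λ = 0.04 × 68 × 2/0.5 = 10.88, df 1 and 66, critical F = 3.986, power 90.15%.
- N = 66: λ = 10.56, power 89.3%.

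With equal groups, 68 is therefore the smallest total that reaches 90%, for **one** endpoint at an unadjusted 0.05. Other inputs give other totals: 94 at ρ = 0.3 and 42 at ρ = 0.7 (both m = 2), and 56 with m = 3 and ρ = 0.5.

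**2. False positives if any one of four suffices, each tested at 0.05.** Under independence the rate is 1 − 0.95⁴ = 18.5%. For two-sided tests on jointly normal statistics this is the maximum (Šidák inequality). With no distributional assumption the bound is 4 × 0.05 = 20%. For correlated endpoints, write Zⱼ = δ + √r·U + √(1−r)·Eⱼ with standard normal U and Eⱼ, and integrate over U. The null case is δ = 0.

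**3. Power, taking 90% per endpoint.** Here δ = 1.960 + 1.282 = 3.242 for every endpoint. Under independence, all-four power is 0.9⁴ = 65.6% and any-of-four power is 1 − 0.1⁴ = 99.99%.

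| r | Any-of-four false positive | All-four power | Any-of-four power, unadjusted |
|---|---|---|---|
| 0 | 18.5% | 65.6% | 99.99% |
| 0.3 | 17.4% | 70.5% | 99.7% |
| 0.5 | 15.6% | 74.1% | 99.1% |
| 0.7 | 13.0% | 78.3% | 97.8% |
| 0.9 | 9.4% | 83.7% | 95.1% |

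**4. Effect of an adjustment.** Holm's first step is 0.05/4 = 0.0125, with critical F = 6.595 on 1 and 66 df. Power for one endpoint at N = 68 and m = 2:

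| ρ | λ | Power at 0.05 | Power at 0.0125 |
|---|---|---|---|
| 0.3 | 7.77 | 78.4% | 58.9% |
| 0.5 | 10.88 | 90.2% | 76.5% |
| 0.7 | 18.13 | 98.7% | 95.1% |

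At ρ = 0.5, restoring 90% at 0.0125 takes 94 analysed (90.6%; 92 gives 89.8%). That is more than the 79 participants the Abstract reports as randomised.

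**The case against.** The strongest reply is that this is a condensed article. A multiplicity procedure is often left to a statistical analysis plan, and none is shown here, so silence on it is not itself an error. That stands. What the article does publish is a sample size built on an unsplit alpha. If an unseen plan divided alpha, the 90% would no longer describe the tests as run. If it required all four endpoints, the 90% would not describe the claim. Either way the published power needs a label.

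Several stronger readings are tempting, and the documents do not support them.

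- **A reader might infer that the protocol lets any one endpoint count.** It does not say so. Running the models independently describes how they are fitted, not how success is decided, and 0.05 appears only in the sample size sentence. Its use for each test is inferred from the separate models and the absence of any split. The hypothesis, if anything, leans towards all measures improving. The 18.5% is therefore conditional on the claim made.
- **A reader might infer that power is short under either rule.** It is not. If all four effects are real, unadjusted any-of-four power is above 90% throughout the table. Only the all-four claim falls short.
- **A reader might count the ACE split times as further primary tests.** The article says only that they are measured. Total time is also made up of its splits, so treating them all as independent tests would be wrong.

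It is also fair to say that the four endpoints cover different domains and that effect estimates with intervals are planned. This softens the consequence but does not supply a rule.

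**Conclusion.** The point holds in conditional form. The article fixes four co-equal primary endpoints, separate models and a single unsplit 0.05, and leaves open what result would count as success. If any one significant endpoint may be claimed, the family-wise false-positive rate is up to 18.5%, and still 13.0% at an endpoint correlation of 0.7. If all four are needed, the error rate is controlled and joint power is about 66% to 84%. The stated 90% corresponds to one endpoint at an unadjusted 0.05.

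The error rates rest on approximate joint normality and an assumed common correlation. The joint power also assumes 90% for each endpoint. The reading of the 90% as a single-endpoint figure rests on an exact reproduction of 68 under m = 2 and ρ = 0.5, neither of which the article states. That no rule is stated does not depend on any of these assumptions.

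**What to change.** Before the final analysis, choose one of two rules and state it.

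1. **Separate claims.** Apply Holm at an overall two-sided 0.05 across the four primary group-by-time tests, and claim benefit only for endpoints that survive. This keeps the interaction that section 2.9 already names as the term of interest.
2. **Joint claim.** State that success requires all four endpoints to be significant at 0.05, and restate joint power as about 66% to 84%, depending on how correlated the endpoints are.

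Under either rule, name one ACE variable as primary (for example total time) and make the split times secondary. Describe the 90% as power per endpoint at an unadjusted 0.05, and give the number of measurements and the repeated-measures correlation behind it.

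The change takes a few sentences and needs no new participants or measurements. The cost of the first option is power: at Holm's first step, about 77% per endpoint with 68 analysed under the assumptions that reproduce the plan. Holm cannot do worse than this first-step figure for given inputs, but the figure itself runs from 59% to 95% for repeated-measures correlations of 0.3 to 0.7, so it is not a guaranteed floor. The cost of the second option is that one failed endpoint defeats the claim.

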### 2.5. Primary Endpoints

According to the main components of the agility training approach, we selected neuromuscular measures of strength, balance and motor performance as primary outcomes. Maximum knee extension strength is measured under isometric conditions. Therefore, participants are seated in a leg extension machine (Edition-Line, gym80, Gelsenkirchen, Germany) that is equipped with a force transducer (mechaTronic, Hamm, Germany) with a hip angle of 90° and a knee angle of 120°. Participants are instructed to push as hard and as fast as possible against a pad that is placed above their ankle joints and to keep pushing for two to three seconds, following current recommendations on instructions for strength testing [23]. Maximum strength (Fmax) and the rate of force development (RFD) are computed by the measurement/analysis software IsoTest (version 2.0, meachTronic, Hamm, Germany). Thereby, Fmax serves as a primary outcome. Participants perform three trials, of which the best two are averaged for further data analysis. This testing procedure revealed high reliability for Fmax testing (r = 0.81) [24].

Reactive balance performance is tested barefoot on a two-dimensional platform (Posturomed, Haider Bioswing, Pullenreuth, Germany) as postural sway upon perturbation. The platform, which is mounted on eight springs, is initially fixed in a stable position. A lateral shift from the neutral position for 3.6 cm is initiated. After participants have taken a stable, two-legged, shoulder-wide stance with the hands on the hips (akimbo), slight knee flexion gazing a fixed spot on the wall (at 1.5m distance, 1.75m height), the fixation is suddenly and unexpectedly released after 2 to 5 s. Participants are initially instructed to reduce the induced pendular movement as fast as possible, and remain a stable position for 10 s. An acceleration sensor (MicroSwing® 6, Haider Bioswing, Pullenreuth, Germany) captures the amplitude of the pendular movement at 50 Hz. The total sway of the platform over 10 s is calculated and reported in mm (DigiMax Posturomed, Software Version 1.0, mechaTronic, Hamm, Germany). After one familiarization trial, participants perform two trials, of which the best is used for further analysis. Failed attempts are noted as seconds until failure. Overall reliability of unexpected perturbed balance measurements was reported as good (interclass correlation (ICC) = 0.75–0.89) [25].

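### The printed 5% and 90% describe one primary endpoint, but the plan has four unranked ones and no rule for turning four tests into a trial result

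*Protocol article*

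**What the plan says.** The Abstract lists four primary endpoints on an equal footing: "Knee extension strength, reactive balance, dual task gait speed and the Agility Challenge for the Elderly (ACE) serve as primary endpoints". Section 2.5 explains the choice ("we selected neuromuscular measures of strength, balance and motor performance as primary outcomes") and defines each of the four without ranking them.

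Section 2.9 contains one sample size calculation. It refers to the primary outcomes in the plural, "assuming moderate effects (f = 0.2) for training-induced changes in the primary outcomes", with one set of error rates, "statistical power 90%, two-sided significance level α=.05". It concludes that "68 participants (34 per group) are needed for statistical analysis". The primary analysis is described as "Independently conducted two-factorial repeated measured analyses of co-variance (rANOVA", one model per endpoint, with the group-by-time interaction as the term of interest.

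The article gives no hierarchy, division of alpha, global test or statement of how many endpoints must succeed.

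**The concern.** With four primary tests, the error rate and the power of the trial depend on what counts as success. Two rules are common:

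- **Any one of four.** A single significant endpoint supports a positive conclusion. The chance of a false positive trial then exceeds 5% unless alpha is shared.
- **All four.** A positive conclusion needs every endpoint. The 5% is then safe without adjustment, but the chance of winning all four is below the chance of winning one.

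The plan prints a single 5% and a single 90% and names no rule. If both figures belong to one endpoint, at least one of them does not describe the trial under either rule. The rule could also be settled after the results are known. Section 4 hopes that the results will establish the training approach and carry it to coaches, so what counts as a positive result matters.

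**Working it through.** **Inputs from the article.** Four primary endpoints (Abstract, 2.5); alpha 0.05 two-sided, power 90%, f = 0.2, N = 68 as 34 per group (2.9).

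**Inputs not stated, so assumed.** Number of time points m and correlation ρ between repeated measures in the G*Power calculation; correlation r between the four endpoint tests, taken as equal for all pairs and varied from 0 to 0.8.

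**Step 1: reproduce N = 68.** For a within-between interaction with two groups and sphericity, λ = f²·N·m/(1 − ρ), with degrees of freedom (m − 1) and (N − 2)(m − 1). With m = 2 and ρ = 0.5:

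- N = 68: λ = 0.04 × 68 × 2 / 0.5 = 10.88; df 1 and 66; power 90.15%.
- N = 66: λ = 10.56; power 89.3%.

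So 68 is the smallest even total that reaches 90%, for one endpoint at the full 5%. Other settings tried do not give 68: m = 3 with ρ = 0.5 gives 56, m = 2 with ρ = 0.3 gives 94, and m = 2 with ρ = 0.6 gives 56.

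**Step 2: four tests at 5% with 90% power each.** Under independence:

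- At least one false positive: 1 − 0.95⁴ = 18.5%.
- All four significant when all effects are real: 0.9⁴ = 65.6%.
- At least one significant when all effects are real: 1 − 0.1⁴ = 99.99%.

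For correlated tests I used simulated equicorrelated normal statistics, with mean 1.960 + 1.282 = 3.24 under the planned effect:

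| r | Any false positive | Power, all four | Power, at least one |
|---|---|---|---|
| 0 | 18.5% | 65.6% | 99.99% |
| 0.3 | 17.4% | 70.4% | 99.7% |
| 0.5 | 15.6% | 74.1% | 99.1% |
| 0.8 | 11.4% | 80.7% | 96.7% |

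Without any assumption on dependence, the error bound is 4 × 5% = 20%. The trial-level figures equal 5% and 90% only if the four tests are perfectly correlated.

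**Step 3: power if alpha is shared.** Holm's first step uses 0.05/4 = 0.0125.

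- Interaction formula at alpha 0.0125 with N = 68, m = 2, ρ = 0.5: 76.5%.
- Normal approximation, starting from exactly 90% at 5%: about 77% under Holm for an endpoint that is the only one affected.
- Holm average per endpoint when all four effects are real: about 87% at r = 0, falling to about 84% at r = 0.8.
- Sensitivity at alpha 0.0125, N = 68, f = 0.2: 59% at ρ = 0.3 and 95% at ρ = 0.7 with two time points; 87.7% with three time points and ρ = 0.5.

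**The case against.** Several points on the other side are fair.

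**The SAP is not shown.** A multiplicity rule may be written there, and the article nowhere says that the tests will be unadjusted. Separate models per endpoint are compatible with a Holm step afterwards. That stands, so the absence of a rule alone is not the point. What remains is that alpha, power and N are fixed in section 2.9 and reproduce as a single test at the full 5%. A later alpha split would leave the printed 90% wrong for the adjusted tests.

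**Power of 90% for each endpoint is not printed.** Correct. It is inferred from the reproduced N, which itself rests on two inferred inputs.

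**Four separate claims.** If each endpoint answers its own question, 5% and 90% correctly describe each test, and whether family-wise control is needed is debatable. This is a legitimate position, but the article does not take it, and the figures would still need the label per endpoint.

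**Stronger readings that a reader might infer.** One is that the trial has both an inflated error rate and too little power. The two cannot occur together: under any-of-four, power for at least one endpoint exceeds 90%, and under all-of-four the error rate is not inflated. Another is that the Introduction already requires all four, since it expects "the agility training approach induces notable improvements in all physical performance measures". That sentence also covers aerobic capacity, which is assessed among the secondary endpoints (2.6.3). It is a broad expectation and not a decision rule for the four primaries.

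**Conclusion.** The concern holds in limited form and should be fixed. The 5% and 90% are per-endpoint figures, and the article does not say which trial-level rule applies.

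- Any one of four: family-wise error about 11% to 18.5% (r from 0.8 to 0; 20% at most), with power for at least one endpoint above 90%.
- All four: error controlled at 5%, joint power about 66% to 81% (r from 0 to 0.8). A trial in which every assumed effect is real would miss its claim between about one time in three and one in five.

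These ranges assume 90% power per endpoint and jointly normal, equally correlated tests. The adjusted power figures also depend on the design inputs behind N = 68. Section 2.9 names three time points where two reproduce the number, and its model includes a baseline covariate that the formula omits. They should therefore be quoted as a range. The documents do not support saying that the trial will be analysed without any adjustment, only that its printed figures leave no room for one.

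**What to change.** In section 2.9, choose one rule before the analysis and make the figures match it.

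**Preferred.** Apply Holm across the four primary group-by-time interaction tests at a family-wise two-sided 5%, and claim each endpoint on its Holm-adjusted p-value. Label the 90% as per endpoint before adjustment. Restate power as about 77% for a sole affected endpoint, given 90% at the unadjusted 5%, and about 84% to 87% per endpoint on average if all four effects are real. Show the assumptions: at alpha 0.0125 with N = 68, f = 0.2 and two time points, power runs from 59% to 95% over repeated-measures correlation 0.3 to 0.7, and is about 88% with three time points at 0.5. Report unadjusted estimates and intervals alongside.

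**Alternative.** State that all four must be significant at 5%, leave alpha unadjusted, and state joint power of about 66% to 81%.

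**Cost.** A few sentences and a less favourable power figure. Holm slightly lowers power per endpoint when all four effects are real, and more so when only one is. No new data or participants are needed.

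### Baseline is both covariate and first time level, and the group-by-time interaction is the main term, so for three of four primary endpoints the main test is not the one-year group difference.

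*Protocol article*

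**What the plan says.** Protocol article, section 2.9, fixes three features of the primary analysis, which is run separately for each endpoint:

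- The covariate: "with the respective endpoint as a baseline measure serving as the covariate".
- The time factor: "factor 2: time point of measurement; baseline, interim, post".
- The decisive term: "The rANOVA interaction term between both factors is the main term of interest".

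The same section plans change scores for T1–T3, T1–T2 and T2–T3 with 90% confidence intervals, but as estimates of effect size and not as tests. The sample size statement reads "68 participants (34 per group) are needed for statistical analysis", "assuming moderate effects (f = 0.2) for training-induced changes in the primary outcomes", with 90% power and a "two-sided significance level α=.05".

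The Introduction puts the one-year comparison with the inactive control group first. Effects visible at six months that keep growing are the second hypothesis. Section 2.7 lists leg extension strength, dual-task gait speed and perturbed balance at the interim assessment. It does not list the Agility Challenge for the Elderly (ACE).

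**The concern.** The T1 value stands on both sides of the model, and section 2.9 does not settle what the covariate then does. If it enters only as a main effect, it cannot change a within-person interaction in complete data, so the main term is unadjusted for baseline. If it is crossed with time, the interaction becomes a baseline-adjusted joint test of T2 and T3. These are different tests with different power.

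Under either reading, three time levels give the interaction 2 degrees of freedom. It answers whether the groups differ in time course anywhere, not whether they differ at one year. It can be significant without any one-year benefit, and it spends a degree of freedom that the one-year question does not need.

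The ACE is a separate difficulty. With no T2 value listed, the stated three-level model cannot be fitted for this primary endpoint.

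**Working it through.** **Inputs from section 2.9:** f = 0.2, two-sided alpha 0.05, power 90%, N = 68 (34 per group). **Assumed, because the article does not give them:** equal variances, one common correlation ρ between time points (0.5 unless stated), sphericity, complete data, and the effect patterns in SD units.

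**1. The plan's own figure.** For a within-between interaction with m time points, λ = f²·N·m/(1−ρ), with df (m−1) and (N−2)(m−1).

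- m = 2: λ = 0.04 × 68 × 2/0.5 = 10.88 on 1 and 66 df; power 0.902. N = 68 is reproduced.
- m = 3: λ = 0.04 × 68 × 3/0.5 = 16.32 on 2 and 132 df; power 0.956. N = 56 would be enough.

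So 68 fits a pre–post comparison at ρ = 0.5. This suggests but does not prove a two-point calculation: at ρ = 0.4, three levels need 66.

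**2. Difference implied by f = 0.2 (two time points).** The change-score test has λ = (N/4)·D²/[2(1−ρ)]. Setting 17·D²/1 = 10.88 gives D² = 0.64, so D = 0.8 SD. With m = 2 this does not depend on ρ.

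**3. Interaction with the covariate as main effect.** λ = (N/4)·SS/(1−ρ), where SS is the sum of squared deviations of the three group differences (0, d₂, d₃) from their mean; df 2 and 132.

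- Steady gain (0, 0.4, 0.8): SS = 0.32, λ = 17 × 0.32/0.5 = 10.88; power 0.84. The noncentrality equals that in step 1 for m = 2, so the fall from 0.90 comes from the second degree of freedom.
- Six-month effect only (0, 0.8, 0): SS = 0.64 − 0.64/3 = 0.427, λ = 14.51; rejection 0.93.

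**4. Baseline-adjusted T3.** λ = (N/4)·d₃²/(1−ρ²), df 1 and 65. For d₃ = 0.8: 17 × 0.64/0.75 = 14.51; power 0.96. For d₃ = 0, rejection is 0.05 by construction.

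**5. Simulation, which also covers the covariate crossed with time** (34 per arm, ρ = 0.5, 4,000 to 10,000 runs per pattern; ranges span separate runs):

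| Effect at T2 / T3 (SD, assumed) | Interaction, covariate main effect | Interaction, covariate × time | Adjusted T3 |
|---|---|---|---|
| 0 / 0 | 5% | 5% | 5% |
| 0.8 / 0 | 93–94% | 95–96% | 5% |
| 0.4 / 0.8 | 83–84% | 90–91% | 96% |
| 0.25 / 0.5 | 42–43% | 50–51% | 63–64% |
| 0.5 / 0.5 | 55–56% | 66% | 65% |

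At ρ = 0.7, the 0.25/0.5 pattern gives about 64–65%, 69–70% and 80%, and for 0.4/0.8 all three exceed 96%.

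**6. ACE.** With T1 and T3 only and the covariate crossed with time, the 1-df interaction is the one-year analysis of covariance. The mismatch of target does not arise there; the model wording is still wrong for it.

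**The case against.** The strongest defence is that section 2.9 gives the primary analysis the purpose of comparing time courses, and that the second hypothesis concerns exactly that. With randomised groups, the interaction's null is no group difference at T2 or T3, so it is a less targeted test of benefit and not an irrelevant one. This stands, but it does not supply a test for the first hypothesis.

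The T1–T3 change score with its interval would also expose a benefit that had faded, and such fading runs against what the authors expect. That is true. The interval is nevertheless planned as an estimate beside two others, and the declared test would still be positive.

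Whether the covariate is crossed with time could be settled in a fuller plan. That is fair, and it is why both readings are shown. Neither makes the interaction a one-year test when there are three time levels.

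A reader might infer more than the article supports:

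- **That using baseline twice inflates the type I error.** It does not; the level is about 5% under the global null.
- **That a benefit complete at six months and then maintained would be missed.** This would follow only if baseline were dropped from the time factor while the interaction stayed the main term. The article keeps three levels, and for that pattern they lose little or nothing with the covariate crossed with time (66% against 65% at 0.5 SD), and about 10 points with a main effect only.
- **That power is severely reduced.** The large losses belong to an assumed 0.25/0.5 SD pattern, which is smaller than the 0.8 SD implied by f = 0.2.

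**Conclusion.** The concern holds as a mismatch between the declared main test and the first hypothesis, for three of the four primary endpoints. For the ACE, the stated model cannot be fitted as written.

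At about the plan's own effect size, reached by a steady gain, the cost is roughly 5 points of power (covariate crossed with time) or 12 points (main effect only) at a correlation of 0.5. It is negligible at higher correlations and larger for smaller effects. The more important weakness is interpretive: a significant main term does not establish a one-year benefit, as the six-month-only pattern shows.

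These sizes rest on assumed correlations, compound symmetry, complete data and assumed effect patterns. The structural point rests only on the wording of section 2.9, section 2.7 and the Introduction. Severity: should be fixed. The test is valid, and the T1–T3 change is at least estimated.

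**What to change.** Make two changes together:

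1. Take baseline out of the time factor. For the three endpoints with interim data, model T2 and T3 as responses, with baseline (crossed with time), group, time and group-by-time.
2. Name the baseline-adjusted group difference at T3 as the primary test for each primary endpoint. For the ACE, use an analysis of covariance at T3.

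Keep the T2 difference and the T3-minus-T2 contrast as secondary tests of the time-course hypothesis.

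The first change must not be made alone. With only T2 and T3 as levels, an interaction kept as the main term would test whether the group gap changes between them, and would have about 5% power for a constant effect of any size.

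The cost is wording, settled before T3 data are analysed. The omnibus time-course test becomes secondary. No extra participants are needed for this change: 68 analysed give about 96% power for 0.8 SD at T3 with correlation 0.5.
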